The industrial area of Birlagram Nagda in the central Indian state of Madhya Pradesh (MP), has been under scrutiny due to the pollution emanating from the multiple viscose rayon textile and associated chemical manufacturing industries operating in the area [15]. As per data compiled by the Central Pollution Control Board (CPCB) [16] in 2013, the apex government run agency monitoring environmental pollutant concentrations in the country, the area has a comprehensive environment pollution index score of 66.67, which indicates that it is among the “severely polluted” industrial clusters in India. Although recent statistics have shown improvement in the area’s pollution index, it is still listed in the top hundred polluted industrial clusters in India [17]. Major chemical pollution associated with viscose rayon textile manufacturing occur secondary to gaseous emission of carbon disulphide (CS_2_), Hydrogen Disulphide (H_2_S), Hydrogen Chloride (HCl), Chlorine (Cl_2_), Sulphur oxides (SO_2_ and SO_3_) and untreated discharge of viscose fibre wastewater effluent containing high concentration of heavy metals, and other toxic substances into natural water sources [9]. However, there is hardly any scientific evidence regarding the health effects of residing near the industries of Birlagram. Considering the growing health concerns of the local public, regulatory authorities in India directed the industries operational in the region to implement pollution control strategies as well as commissioned detailed environmental and health-oriented investigation of the issue [18]. The current study was initiated as per directions of the local authorities to evaluate the health effects of exposure to multiple pollutants emitted from the industrial activity in Birlagram. Specifically, the objectives of the current study include:

To measure the concentration of gaseous pollutants (i.e. CS_2_, H_2_S, HCl, Cl_2_, and SO_2_) in the ambient air in the study area.To measure the concentrations of heavy metals and anions [i.e. lead (Pb), mercury(Hg), aluminium (Al), chloride (Cl^-^) and sulphate(SO_4_^2-^)] in groundwater samples.To determine the association between the concentration levels of pollutants in air and water samples with that in bio-samples (blood and urine).To identify the association between exposure to pollutants and health effects in study participants.

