#### Human exposure assessment

Following biomonitoring will be done to assess exposure in the selected participants:

*i) Inhalational CS*_*2*_
*exposure*. Iodine-azide test will be carried out for estimation of CS_2_ exposure of the participants. The iodine-azide test is based on the fact that certain constituents in the urine of persons exposed to CS_2_ catalyze the reaction between iodine and sodium azide [34, 35]. Participants will be asked to provide approximately 50 mL of clean catch spot urine sample in a sterile container which will be stored at -20°C till analysis. Preparation of reagents and buffers as well as the test procedures will be carried out as previously described [34, 36]. The exposure coefficient will be calculated to estimate Carbon disulfide exposure.

*ii) Metal (Pb*, *Hg and Al) exposure*. Blood levels of Pb, Al, and Hg will be examined in a sub-group of the studied population (sample from every tenth participants). For this, 1 mL of whole blood from each participant will be mixed with 6 mL of freshly prepared mixture of concentrated trace metal grade HNO_3_ and hydrogen peroxide (H_2_O_2_) in a ratio 2:1 (v/v) in high-purity polytetrafluoroethylene (PTFE-TFM) vessels. After gentle mixing of reactants, the PTFE-TFM vessels will be arranged in the rotor (24HVT80, Anton PAAR) and digestion will be carried out in the Anton Paar, Multimicrowave PRO Reaction System at 200°C for 15 minutes [37]. After digestion, the solutions resulting from each digested samples will be cooled to 40°C and diluted to 30 mL with distilled water. Blank will also be prepared for each cycle of digestion using distilled water, nitric acid, and hydrogen peroxide mixture. Analysis of Pb, Al and Hg in the digested blood samples will be carried out on ICP-OES (iCAP**®** 7400 Duo ICP-OES, ThermoFisher Scientific**®** Pvt Ltd) system using same run parameters as used for groundwater analysis. Recorded metal levels in each sample will be tabulated in ppb levels.

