#### Data management and analysis

All participants’ data will be coded by assigning unique identifiers. These codes will be used to identify and link various parameters of the individual participants. Data from the filled questionnaires/clinical proforma as well as the laboratory analysis values will be entered into the latest version of Microsoft Excel spreadsheets. Statistician of the team will supervise data entry and to ensure error-free data at least 10% of the entered data will be randomly verified.

Once data entry is complete, hard copies of questionnaire/proforma will be stored in a secure archive in the institute. Similarly, all entered data will be stored in password protected computer systems with access restricted to the research team alone. The data collected/generated in this study will be stored for a period of ten years. The primary investigator will be in-charge of data safety and back-up maintenance. Anonymized data set will be shared publicly during publication of study results.

All statistical analyses will be performed using IBM SPSS Statistics (version 25). For ordinal and continuous variables, the values will be given as descriptive statistics (like mean, median, standard deviation, 95% confidence interval, interquartile range); and categorical variables will be given as numbers (percentages) and proportions. Association for different health aspects with pollution level of various parameters of air/water will be made using Pearson’s chi-square test for independent categorical data. By considering the variability within and between groups; t-test and ANOVA will be used to analyze the mean differences between two and more groups respectively for various anthropological parameters, the concentration of air/water pollutants, etc. The Mann–Whitney U test and Wilcoxon signed ranks test will be used for independent and dependent for ordinal and continuous data with respect to different health aspects. Pearson and Spearman’s correlation coefficient will be used to examine the association between different variables. Multiple linear and logistic regression models will be used to estimate the relationship for different neurological assessments with a set of the independent variable. For all statistical tests, two-sided P-values <0.05 will be considered to be significant.

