Industrial pollution is a multidimensional issue since it occurs in multiple environmental matrices and in turn affects multiple organ systems in the human. Therefore, in our study we will focus on multiple objectives with an overarching goal to assess the potential health effects of exposure. A major strength of this study is therefore its multidisciplinary research team with expertise of investigators ranging from health sciences like epidemiology and neurology to environmental sciences and basic science. To strengthen the association between pollutant concentration in environmental matrices and health effects, human exposure assessment will be done in a subset of the population to ascertain dose-response relation. Therefore, exposure to CS_2_ will be confirmed using the urine azide test which has been reported to adequately reflect occupational CS_2_ inhalation by published literature [34–36]. Furthermore, blood levels of heavy metals will also be determined to estimate exposure of villagers to toxic metals, viz. Pb, Al and Hg from various environmental matrices, viz. air, water and food/soil. However, pertaining to resource limitation, biomonitoring will be conducted in a subset of the total study population.

The current study also faces certain limitations. Long term follow-up of the participants to establish a temporal relationship between exposure and outcome is not possible in our cross-sectional study. Considering the ongoing dispute between local residents, viscose rayon manufacturers and the local authorities, the current study prioritised timely delivery of baseline health effect information. Future research might therefore focus on longitudinal data collection on the environmental health effects of viscose rayon manufacturing. Furthermore, past exposure assessment will be done through questionnaire data and is therefore, prone to recall bias. Although data will be collected for multiple relevant confounders including other environmental/meteorological, socioeconomic and diet/lifestyle factors, the risk of residual confounding cannot be completely eliminated.

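### Biomonitoring is justified by dose-response, but no analysis sentence ties the biomarkers to a health outcome, and adjusted regression is stated only for neurological assessments

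*Protocol article*

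**What the plan says.** All references are to the protocol article.

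- **Purpose.** The Discussion states that "human exposure assessment will be done in a subset of the population to ascertain dose-response relation". The section Human exposure assessment introduces the urine iodine-azide test (giving a CS2 exposure coefficient) and blood Pb, Hg and Al with "Following biomonitoring will be done to assess exposure in the selected participants"; the metals are measured in every tenth participant.
- **Objectives.** The Introduction gives the bio-samples one objective of their own, which is to relate air and water concentrations to concentrations in blood and urine. The last objective is "To identify the association between exposure to pollutants and health effects in study participants"; it does not say which exposure measure is meant.
- **Analysis.** Data management and analysis has one sentence that names both exposure and health. It begins "Association for different health aspects with pollution level of various parameters of air/water will be made using" and then names Pearson's chi-square test for categorical data. Besides this it plans t-tests, ANOVA and rank tests, and a general line: "Pearson and Spearman’s correlation coefficient will be used to examine the association between different variables". Multiple linear and logistic regression is planned to "estimate the relationship for different neurological assessments with a set of the independent variable". The independent variables are not named.

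**The concern.** The stated reason for collecting the biomarkers and the stated analysis do not meet. A dose-response claim needs an estimate of how the outcome changes with a person's exposure, adjusted for what else drives both. The one explicit exposure-health test does not supply this. Pearson's chi-square treats exposure categories as unordered, gives no slope and adjusts for nothing. Its exposure is an area value: air is monitored at sites, with one representative site where sites cluster, so many people share one figure. Such a comparison cannot separate the pollutant from other differences between villages, such as wealth or diet.

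At stake is whether the study can report an adjusted, individual-level exposure-response for its cardiac, respiratory and blood pressure outcomes, although the data for it will be in hand.

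**Working it through.** **1. The plan's own figure.** From Sample size calculation: p = 0.26, q = 0.74, z = 1.96, R = 0.30, Deff = 1.25, d = 0.02.

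n = 1.96² × 0.26 × 0.74 × 1.30 × 1.25 / 0.02² = 3002.69, rounded up to 3003. This matches. The outcome behind it is ECG abnormality.

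**2. Which analysis sentence can carry a biomarker-to-health analysis?**

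| Analysis sentence | Exposure named | Outcome named | Adjusted? |
|---|---|---|---|
| Chi-square | air/water level | health aspects, as categories | no |
| t-test, ANOVA | none | anthropological parameters, pollutant concentrations and the like | no |
| Rank tests | none | health aspects | no |
| Correlation | none (unspecified variables) | none | no |
| Multiple linear/logistic regression | none (unspecified set) | neurological assessments | yes |

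The CS2 coefficient and the blood metals appear in no row. They could enter the correlation row for any outcome, and the regression row for neurological outcomes. For ECG, spirometry and blood pressure, no row gives an adjusted estimate, whether the exposure is a biomarker or an area level.

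**3. Would an individual-level analysis be feasible?** Assumptions: 80% power (not in the article), two-sided 0.05 (in the article), and no allowance for clustering or covariates. The article does not give the number of people with a CS2 coefficient, so only the metals are sized.

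- Number with metals: 3003/10, about 300, if all 3003 take part. If 3003 are invited and 3003/1.3 = 2310 respond, about 231.
- Detectable correlation (Fisher z): r = tanh[(1.960 + 0.842)/√(n − 3)].
  - n = 300: tanh(2.802/√297) = 0.16
  - n = 231: tanh(2.802/√228) = 0.18
- Detectable odds ratio for ECG abnormality per SD of the biomarker: OR = exp[2.802/√(n × 0.26 × 0.74)].
  - n = 300: exp(2.802/√57.72) = exp(0.369) = 1.45
  - n = 231: exp(2.802/√44.44) = exp(0.420) = 1.52

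The analysis is feasible with modest precision.

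**The case against.** The strongest reply is that this is missing detail, not error. The document is a condensed article, and which biomarker enters which model is commonly left to an analysis plan. The correlation and regression sentences are not limited to air and water levels, and the section links each participant's data by code. Dose-response is also not the samples' only purpose: they have their own objective against air and water levels, which the correlation sentence can serve, and the Discussion also uses the urine test to confirm CS2 exposure.

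Much of this stands. A reader might infer that the plan uses only area levels for health outcomes and that the individual dose-response will not be delivered. The text does not support that, because it neither assigns the biomarkers to a health outcome nor excludes them.

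Two further inferences also fail:

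- **A stated share of exposure contrast lost at area level.** This would need the between-village share of biomarker variance, which the article does not give. Any percentage would only restate an assumption.
- **Taking each person's deviation from the village mean as the dose-response result.** That would remove the between-village contrast by distance, wind and river on which the design rests. Blood metals also reflect food and soil according to the Discussion, so the remaining variation may be largely non-industrial. The term would still be open to individual confounding.

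The reply does not reach what the article does fix: an unadjusted area-level chi-square as its one explicit exposure-health test, and regression stated for one outcome family only.

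**Conclusion.** The point holds as a mismatch between the stated purpose and a poorly fixed method. No analysis sentence ties the CS2 coefficient or blood Pb, Hg or Al to a health outcome, although dose-response is given as a reason for measuring them. Followed as written, ECG abnormality, spirometry and blood pressure receive no adjusted exposure-response estimate. This conclusion rests on the wording alone. The sample size figure is correct and not in question. The power figures show only that a better analysis is feasible; they depend on the assumed 80% power and would be less favourable after clustering and adjustment.

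**What to change.** In Data management and analysis:

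1. Extend the multiple linear and logistic regression to ECG abnormality, FEV1, FVC and blood pressure, alongside the neurobehavioural scores.
2. Name the individual biomarkers (log blood Pb, Hg and Al; the CS2 coefficient) as exposures, in participants who have them.
3. Adjust for age, sex, smoking, schooling and occupation, and allow for village. The article plans to collect demographic, socioeconomic, lifestyle and occupational data; I take smoking and schooling to be covered by these.
4. Label results based on air and water levels as area-level associations.
5. If wanted, report a split into village mean and individual deviation as a supplementary analysis, not as the only dose-response result.

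The cost is a few sentences and extra analysis of data already planned and linked. The downsides are the modest precision shown above and the number of tests. Four biomarkers against five outcomes, counting blood pressure and the neurobehavioural battery once each, is 4 × 5 = 20. At 0.05 that gives an expected 20 × 0.05 = 1 false positive if no association exists. The report should say so and lead with estimates and intervals.

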#### Health assessment

Following health-related data will be collected from all selected participants:

*i) Questionnaire-based collection of data on demography*, *exposure and lifestyle*. A structured questionnaire which has been developed by the researchers will be pilot-tested and thereafter wards used for collection of socioeconomic and demographic details along with information regarding lifestyle factors, occupational and relevant exposure history. The questionnaire will be administered by trained investigators in the local language.

*ii) Anthropometry and blood pressure monitoring*. Height and weight will be measured using stadiometer and weighing scale, respectively and will be used to calculate body mass index (BMI). As per guidelines for Indian population [38], BMI in the range of 18.5–22.9 kilogram per square metre (kg/m^2^) will be considered as normal, 23–24.9 kg/m^2^ as overweight and more than or equal to 25 kg/m^2^ will be considered as obesity. Blood pressure will be measured as per the International Society of Hypertension’s 2020 Global Hypertension Practice Guidelines [39] in sitting position on the left arm using validated electronic blood pressure monitor (Omron**®**), after 5 minutes of rest. Systolic and diastolic blood pressure will be recorded as the mean of last two of three readings taken 1 minute apart. Hypertension will be defined as the study participants having raised systolic and/or diastolic blood pressure (more than or equal to 140 and/or 90 millimetres of mercury i.e. mm Hg, respectively) [38].

*iii) Clinical history and examination*. The information regarding current and previous cardiorespiratory and neurological symptoms will be taken by the physicians from the participants using a clinical proforma. The details regarding the onset, duration, severity of symptoms, diurnal variation, aggravating/relieving factors, and associated symptoms details will be noted. A general physical examination and detailed respiratory, cardiological and neurological examination of all participants will be conducted which will include higher mental function examination, speech assessment, cranial nerve examinations, examination of the motor system and muscle power, examination of the sensory system, reflexes and coordination, and gait assessment, etc. All abnormal findings will be recorded in a pre-designed the clinical proforma.

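### Multivariable regression is named for the neurological assessments alone, so the exposure associations for ECG, spirometry, blood pressure, lipids and other laboratory outcomes have no planned confounder adjustment

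*Protocol article*

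**What the plan says.** The section on data management and analysis lists methods by type of comparison.

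- Health against pollution level: "Association for different health aspects with pollution level of various parameters of air/water will be made using Pearson’s chi-square test for independent categorical data".
- Group means: "t-test and ANOVA will be used to analyze the mean differences between two and more groups respectively". The examples given there are anthropological parameters and pollutant concentrations, followed by an open-ended etc.
- Ordinal and continuous data on health aspects: "The Mann–Whitney U test and Wilcoxon signed ranks test will be used for independent and dependent for ordinal and continuous data".
- Association between variables generally: "Pearson and Spearman’s correlation coefficient will be used to examine the association between different variables".
- Multivariable models: "Multiple linear and logistic regression models will be used to estimate the relationship for different neurological assessments with a set of the independent variable".

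Three other places bear on this. The fourth objective in the Introduction is "To identify the association between exposure to pollutants and health effects in study participants", with no restriction to the nervous system. The Health assessment section collects blood pressure, spirometry, ECG, lipids, glucose and blood counts from all participants, and a questionnaire records socioeconomic and demographic details with "information regarding lifestyle factors, occupational and relevant exposure history". The Discussion states that "data will be collected for multiple relevant confounders including other environmental/meteorological, socioeconomic and diet/lifestyle factors" and then lists residual confounding as a limitation.

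**The concern.** Exposure in this study follows where people live, and villages at different distances and directions from the plants may differ in age, smoking, socioeconomic position and employment in the plants. Each of these can affect ECG findings, lung function, blood pressure and lipids. Occupation matters most. The Introduction separates the effect of residing near the industry from occupational exposure, and the eligibility criteria do not exclude plant workers. If workers tend to live closer in, a crude comparison credits to residence what belongs to the job.

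The article goes further than leaving a covariate list open. It states a set of methods in which adjustment is attached to one outcome domain, and this sits badly with its own general objective and its own remark on residual confounding. Followed as written, the fourth objective would have an adjusted answer for the neurological outcomes and a crude one for the rest.

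**Working it through.** **1. Scope of adjustment.** Setting the sections side by side:

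| Element | Neurological assessments | ECG, spirometry, blood pressure, lipids, other laboratory outcomes |
|---|---|---|
| Within the fourth objective | yes | yes |
| Measured in all participants | yes | yes |
| Unadjusted tests listed | yes | yes, as health aspects |
| Multivariable regression listed | yes | no |

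No other section extends regression, stratification or any other adjustment to the right-hand column. Those outcomes are not named in the analysis section. They fall under its general term for health aspects, because the regression sentence does not include them.

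**2. The plan's own figure.** Inputs from the sample size section: z = 1.96, p = 0.26, q = 0.74, R = 0.30, Deff = 1.25, d = 0.02.

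n = z² × p × q × (1 + R) × Deff / d² = 3.8416 × 0.1924 × 1.30 × 1.25 / 0.0004 = 3002.69, rounded up to 3003.

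The stated figure reproduces. It is the precision of a single descriptive prevalence, which needs no confounder adjustment, so this point changes nothing in it.

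**3. Illustration of the bias.** The documents give no confounder distribution by village and no confounder effect, so the following inputs are assumptions. The groups are the 2000 northern and 1003 southern participants, used only because the article gives these sizes. It does not state a north–south test. Overall ECG abnormality is 26%, the true exposure effect is nil and no design effect is applied. One binary confounder has prevalence 30% in the south and 35%, 40% or 50% in the north, with an odds ratio (OR) for ECG abnormality of 1.5, 2 or 3.

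One cell in full (confounder OR 2, 40% v 30%):
- An overall prevalence of 26% requires an abnormality risk of 0.3468 with the confounder and 0.2098 without. The odds are 0.531 and 0.2655, ratio 2.0.
- North: 0.40 × 0.3468 + 0.60 × 0.2098 = 0.2646. South: 0.30 × 0.3468 + 0.70 × 0.2098 = 0.2509.
- Crude OR = (0.2646/0.7354) / (0.2509/0.7491) = 1.07.
- Standard error = √[0.26 × 0.74 × (1/2000 + 1/1003)] = 0.01697, so the expected z = 0.0137/0.01697 = 0.81.
- Two-sided rejection = 1 − Φ(1.96 − 0.81) + Φ(−1.96 − 0.81) ≈ 0.13.

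All cells (crude OR; chance that a nominal 5% test rejects):

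| Confounder OR | 35% v 30% | 40% v 30% | 50% v 30% |
|---|---|---|---|
| 1.5 | 1.02; 6% | 1.04; 8% | 1.09; 15% |
| 2 | 1.04; 7% | 1.07; 13% | 1.15; 35% |
| 3 | 1.06; 10% | 1.12; 25% | 1.25; 70% |

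A mild imbalance does little. A strong confounder with a marked imbalance makes the crude test unreliable. The documents do not say where this study would fall.

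**The case against.** The strongest reply is that the text nowhere excludes regression for other outcomes. It says regression will be used for neurological assessments, and it does not assign ECG, spirometry, blood pressure or lipids to a named test. A journal article condenses a fuller plan, and the remark on residual confounding suggests that the investigators mean to adjust. This stands in part: the article does not record a decision against adjustment, and the detailed covariate list can properly be left to an analysis plan. But the article is not silent. It allocates methods, and the allocation conflicts with its own objective and limitation, so the sentence should be put right.

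Stronger readings are tempting and not supported:

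- A reader might infer that, because the study was sized on ECG abnormality, the sample size or the ECG prevalence is undermined. Neither is, because that calculation concerns one descriptive proportion.
- A reader might set a possible between-zone bias against the 2-point margin of error. The margin is the precision of one overall proportion and is no yardstick for a difference between zones. The article also relates health to pollution level and states no zone contrast.
- A reader might say that spirometry is wholly unadjusted. Predicted FVC comes from a regression equation for each subject, so that outcome is already standardised to an individual reference. This does not deal with smoking or plant work, nor with the fixed FEV1/FVC cut-off.
- A reader might assume that every needed variable is in hand. The article names lifestyle and occupational history as domains, but does not name smoking or plant employment individually.

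**Conclusion.** The point holds as a mismatch of scope. Multivariable regression is stated for the neurological assessments alone, while the fourth objective covers all health effects and the Discussion presupposes adjustment. As written, the exposure associations for ECG, spirometry, blood pressure, lipids and other laboratory outcomes have no planned confounder adjustment and would be open to confounding by age, smoking, socioeconomic position and plant work.

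The size of that bias cannot be determined from the documents. The illustrative range, a crude odds ratio of 1.02 to 1.25 under no true effect, rests wholly on assumed inputs and shows only that the effect can be trivial or serious. The conclusion assumes that the general wording on health aspects covers the outcomes not named, which is the natural reading. The descriptive ECG prevalence and the 3003 are untouched.

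**What to change.** Extend the regression sentence to all health outcomes used for the fourth objective: logistic models for binary outcomes (such as ECG abnormality, hypertension and spirometric impairment) and linear models for continuous ones (such as spirometric volumes, blood pressure, lipids, glucose and blood counts). Use one common covariate set fixed before analysis and drawn from the domains already collected: age, sex, socioeconomic status, lifestyle including smoking, and occupational exposure including plant work. Report the unadjusted tests alongside.

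First confirm that the questionnaire's lifestyle and occupational items record smoking and current or past plant employment. If they do not, items must be added, and the planned pilot test is the time to do it.

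Adjustment for BMI is optional, because BMI may lie on the pathway from exposure to blood pressure or lipids. A sensitivity analysis without plant workers would be a useful extra.

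The cost is a change of wording and a little more analysis work. Sampling and the sample size do not change.
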